### Quality of life scores

The Short Form-36 (SF-36) is a multidimensional measurement of general health. It yields eight domains of functional health and well-being scores. The 'Dutch translated’ Aberdeen Varicose Vein Questionnaire [27] (AVVQ) is a validated disease-specific quality of life measurement for chronic venous insufficiency.

Both questionnaires are completed preoperatively, after 4 weeks, one, two, and five years of follow-up.

### Data collection

Data will be collected at the recruitment centre by means of case report forms. Copies of the case report forms will be sent to the coordinating center (Rijnstate Hospital, Arnhem, The Netherlands) where all data will be entered in a validated data management system (Research Manager, NOVA Business Software, Zwolle, The Netherlands) and controlled by an independent monitor. The participating centers will be informed about the current status of recruitment and adverse events via a newsletter every three months. Additionally, there will be regular contact between the principal investigator and the contact persons from the participating centers.

### Statistical analyses

The study results will be evaluated based on an intention-to-treat analysis. Data concerning the one, two and five year follow-up will be analyzed for both study groups on an intention-to-treat manner by student t-test (normal distribution) of Mann Whitney U-test (skewed distribution). Obliteration rates will be presented as Kaplan Meier curves including censoring.

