### Sample size calculation

The assumption has been made that MOCA will have a similar anatomical and clinical success rate at one year when compared to RFA. For a non-inferiority trial with an effect size (anatomical success) of 93% and a margin of 7%, 210 patients per group are needed (alpha 5%, power 80%). The effect size of 93% refers to an estimated anatomical success rate at a one year follow-up period for both groups. Taking into account 10% dropouts in each arm, 230 patients need to be included in each study arm.

A sample size calculation will also be performed for the second primary endpoint on the hypothesis that MOCA will have lower post-procedural pain, as measured by a 100-point VAS (Visual Analog Scale) score during the first two weeks after surgery. To evaluate a 30% reduction in post-procedural pain, 58 patients per group are needed (alpha 5%, power 80%). This analysis will be performed after the inclusion and randomization of at least all 58 patients in each group.

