### Randomization

Randomization will be performed during the outpatient department visit in which the patient is included. Patients will be randomized by the responsible surgeon to one of the treatment arms, using a web-based randomization tool (Research Manager, NOVA Business Software, Zwolle, The Netherlands). Randomization will be performed by blocks with stratification for participating centers.

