	**Study period**					
	**Screening**	**Procedure**	**4 weeks**	**1 year**	**2 years**	**5 years**
**Outpatient visit**	X		X	X	X	X
**Physical examination**	X		X	X	X	X
**Informed consent**	X					
**Inclusion criteria**	X					
**Randomization**		X				
**CEAP/VCSS**	X		X	X	X	X
**Ultrasound**	X		X	X	X	X
**Pain score**		X				
**AVVQ**	X		X	X	X	X
**SF-36**	X		X	X	X	X

AVVQ: Aberdeen Varicose Vein Questionnaire; CEAP: Clinical Etiology Anatomy Pathophysiology classification; SF-36: Short Form 36-Item Health Survey; VCSS: Venous Clinical Severity Score.

Post-procedural pain is evaluated using a linear VAS score of 0–100 mm during 2 weeks after treatment. After the 4-week control any small branch varicosities may be treated when indicated.

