## Discussion

Since the introduction of minimal invasive modalities for the treatment of great saphenous incompetence, many new techniques have been developed and introduced to the market. While most techniques constantly report anatomical success rates over 90% [13-16], more emphasis is on secondary treatment outcomes such as post-procedural pain, hematoma, quality of life and returning to normal activities. Therefore, the optimal treatment for GSV incompetence is unclear.

The aim of the present randomized trial is two-fold. First, it aims to compare anatomical and clinical success at one year after MOCA, with RFA. Several randomized trials have compared RFA with conventional surgery, endovenous laser ablation and foam sclerosis [12]. These studies showed the superiority of EVLA in terms of anatomical success at one to five years after surgery, although newer radiofrequency devices have similar results [13,28].

Second, it aims to demonstrate that MOCA is associated with a significant reduction in post-procedural pain after treatment. Pain after endothermal ablation is considerable and probably an underreported complication in the literature. Recent studies have shown less post-procedural pain after RFA comparing with EVLA [17,29]. Therefore, accompanied with similar occlusion rates with the newer RFA devices, we have assumed RFA to be one of the 'gold standard’ techniques in minimal invasive treatment for GSV incompetence. In order to have sufficient power, the trial was designed using a non-inferiority principle.

In conclusion, the MARADONA trial is multicenter randomized controlled trial that aims for a reduction in post-procedural pain after MOCA compared with RFA, with a similar anatomical and clinical success.

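### Intention-to-treat is the only named basis for the one-year anatomical non-inferiority claim, and it is not conservative there if patients cross over or are converted

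*Protocol article*

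**What the plan says.** The Sample size calculation section of the Protocol article sets the design: "For a non-inferiority trial with an effect size (anatomical success) of 93% and a margin of 7%, 210 patients per group are needed". It adds that "The effect size of 93% refers to an estimated anatomical success rate at a one year follow-up period for both groups". The error rates are given as "alpha 5%, power 80" percent, without saying whether alpha is one- or two-sided. The Discussion repeats the design: "In order to have sufficient power, the trial was designed using a non-inferiority principle".

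On who is analysed, the Statistical analyses section states: "The study results will be evaluated based on an intention-to-treat analysis". Its next sentence repeats this for the one-, two- and five-year data, and the Abstract says the same. No per-protocol or as-treated set appears in the article.

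Four other statements bear on the point:

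- The Randomization section says: "Randomization will be performed during the outpatient department visit in which the patient is included". Treatment follows as day treatment. Table 1 instead marks randomisation in the procedure column.
- The definitions section makes technical success an endpoint, so technical failure is foreseen. It does not say what happens to such a patient or how the patient is scored.
- The same section defines anatomical success as duplex occlusion of the part of the GSV that was treated, and clinical success as a VCSS gain of at least one point.
- The text below Table 1 says: "After the 4-week control any small branch varicosities may be treated when indicated".

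**The concern.** In a superiority comparison, crossover and non-adherence usually pull the arms together and work against the claim, so intention-to-treat is the cautious choice. That holds for post-procedural pain. In a non-inferiority comparison the same pull works for the claim.

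The case that matters most is a MOCA procedure that fails technically and is completed with RFA. Under intention-to-treat the patient stays in the MOCA arm. Unless a scoring rule says otherwise, a vein closed by RFA then counts as a MOCA success. At stake is a finding that MOCA is within 7 points of RFA when it is not.

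**Working it through.** **Inputs from the article.** Success 93% in both arms, margin 7 points (taken as absolute), alpha 5%, power 80%, 210 per arm, 10% dropout, 230 randomised per arm.

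**Assumed, because the article gives no figure.** Deviation rates of 2%, 5% and 10%; a true MOCA rate of 86%, so that the deficit equals the margin; and one-sided 2.5%.

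**1. Reproduce the sample size.** n = (1.960 + 0.842)² × 2 × 0.93 × 0.07 / 0.07² = 208.6, so 209 per arm. This reproduces 210 and supports one-sided 2.5%. One-sided 5% by the same formula gives 165. One-sided 5% with a pooled null variance gives 211, which also fits, so the sidedness is not certain.

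**2. False non-inferiority.** The claim is made when the lower limit p_MOCA − p_RFA − 1.96 × SE lies above −0.07. The probability of this was obtained by enumerating both binomial distributions with 210 per arm.

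| Assumed deviation | 0% | 2% | 5% | 10% |
|---|---|---|---|---|
| MOCA to RFA, at random: MOCA = 0.86 + 0.07c | 2.9% | 3.2% | 3.7% | 4.8% |
| Two-way crossover: 0.86 + 0.07c and 0.93 − 0.07c | 2.9% | 3.5% | 4.7% | 7.5% |
| Untreated equally in both arms, scored as failure: both rates × (1 − c) | 2.9% | 3.0% | 3.3% | 3.9% |
| Untreated in MOCA only, scored as failure: 0.86 × (1 − c) | 2.9% | 0.7% | 0.06% | 0.0% |

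Hand check by normal approximation, 5% random conversion: MOCA = 0.8635; SE = √(0.93 × 0.07/210 + 0.8635 × 0.1365/210) = 0.0295; (0.07 − 0.0665)/0.0295 − 1.96 = −1.84, which gives 3.3%. The exact figure is 3.7%.

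**3. Conversion of would-be failures.** Suppose every converted patient would have failed with MOCA and then occludes at the RFA rate. MOCA becomes 0.86 + 0.93c.

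- c = 2%: 0.8786, false non-inferiority 10.5%.
- c = 5%: 0.9065, false non-inferiority 42.8%.

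**4. Would an ordinary per-protocol set cure this?** For random deviations, yes: it returns the rate to about 2.9%. For would-be failures, no, because dropping them also raises the MOCA rate.

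- c = 2%: 0.86/0.98 = 0.878 with 206 patients, false non-inferiority 9.6%.
- c = 5%: 0.86/0.95 = 0.905 with 200 patients, false non-inferiority 40.0%.

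If converted patients stay in and count as failures, MOCA remains at 86% and the rate is 2.9%.

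**5. One-sided 5% instead.** The starting value is 5.3%; 10% random conversion gives 8.5% and 10% two-way crossover 12.5%.

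**The case against.** The strongest objection is that the statistical section is three sentences of a condensed article. It does not say that other sets are excluded, and a supportive per-protocol set could sit in the full protocol or analysis plan, neither of which is shown. That stands as far as silence goes. However, the article does more than stay silent: it commits the evaluation to intention-to-treat for superiority and non-inferiority claims alike.

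The second objection is that no conversion from MOCA to RFA is described and no rate is given. This stands. Every figure above beyond the sample size is conditional on an assumed rate, and for random conversion the effect is modest.

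A reader might infer two stronger points that the article does not support.

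- **Every deviation favours non-inferiority.** It does not. Non-treatment confined to the MOCA arm and scored as failure makes intention-to-treat conservative.
- **Branch treatment before one year inflates the non-inferiority claim.** It cannot change occlusion of the GSV, the only endpoint with a margin and a non-inferiority sample size. It can affect VCSS clinical success, but that endpoint has no stated margin, and the article gives no success rate for it and no rate of branch treatment. Any false non-inferiority figure there would rest on invented inputs. Branch treatment is also a permitted step in both arms, not a deviation.

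**Conclusion.** The point holds in limited form. A non-inferiority claim with a 7-point margin rests on intention-to-treat as its only named basis, with no rule for scoring converted, re-treated or untreated patients.

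The size depends on why patients convert. Random conversion of 5% to 10% lifts false non-inferiority from 2.9% to between 3.7% and 4.8%. If 2% or 5% convert because MOCA was failing, and they count as MOCA successes when RFA closes the vein, it reaches about 10% or 43%. These figures assume a true deficit equal to the margin, 210 analysed per arm and one-sided 2.5%. The scoring rule therefore matters more than the choice of analysis set, and a second set that drops converted patients would give little protection.

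The differing times of randomisation in the Randomization section and Table 1 are a smaller, separate inconsistency. They bear on how long patients know their allocation before treatment, and so on how many might go untreated or switch.

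**What to change.** In the Statistical analyses section:

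- Keep intention-to-treat for all endpoints, and as the sole basis for pain.
- For one-year anatomical success, count conversion to the other technique, or re-treatment of the GSV before the one-year duplex, as failure of the allocated arm. State how untreated patients are scored, since a treated segment is undefined for them.
- Add a per-protocol analysis: allocated technique received, one-year duplex done, with converted or re-treated patients kept in as failures.
- Claim anatomical non-inferiority only if the lower 95% limit is above −7 points in both analyses.
- For clinical success, record branch treatment and show the 4-week VCSS, which is already collected, beside the one-year result as a sensitivity display. Do not score branch-treated patients as failures.
- Reconcile the time of randomisation in the text with Table 1.

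**Cost.** One more analysis set, one table and one case report form item, plus some power. The plan states "Taking into account 10% dropouts in each arm, 230 patients need to be included in each study arm"; 230 × 0.9 = 207 per arm, with power 79.7% by normal approximation. Excluding a further 5% leaves 196 and 77.5%. Keeping 210 in the per-protocol set would then need 210/(0.9 × 0.95) = 246 randomised per arm.

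The scoring rule has its own cost if conversions happen only in the MOCA arm, are unrelated to outcome, and are not already reflected in the planned 93%. MOCA at 0.93 × 0.98 = 91.1% against 93% leaves about 51% power with 210 per arm (exact). The expected conversion rate should therefore be stated when the rule is adopted.

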**Discussion:**

The MARADONA trial is designed to show equal results in anatomic and clinical success after one year, comparing MOCA with RFA. In our hypothesis MOCA has an equal anatomic and clinical success compared with RFA, with less post-procedural pain.

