**Figure 1 F1:**
[figure not shown]
**This figure illustrates the study design.** A total of 460 patients will be randomized to radiofrequency ablation (N = 230) or mechanochemical endovenous ablation (N = 230). GSV, great saphenous vein.

After randomization, the GSV is obliterated in day treatment: study arm 1: (RFA); study arm 2: (MOCA).

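### The trial is sized for non-inferiority of one-year anatomical success, but no method named in the analysis section compares that endpoint with the 7-point margin

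*Protocol article*

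**What the plan says.** The Sample size calculation section sets the design: "For a non-inferiority trial with an effect size (anatomical success) of 93% and a margin of 7%, 210 patients per group are needed". It adds: "The effect size of 93% refers to an estimated anatomical success rate at a one year follow-up period for both groups". The Discussion repeats that the design rests on non-inferiority. Primary endpoints places the duplex assessment at one year, and the definitions section makes anatomical success a yes/no outcome (the treated segment is occluded or it is not).

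The Statistical analyses section is the only place where methods are named. Data from the one-, two- and five-year follow-up "will be analyzed for both study groups on an intention-to-treat manner by student t-test (normal distribution) of Mann Whitney U-test (skewed distribution)". Occlusion then has its own sentence: "Obliteration rates will be presented as Kaplan Meier curves including censoring". The section mentions no difference in proportions, no confidence interval and no margin. The 7% figure appears only in the sample size section.

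The abstract words the aim differently: "The MARADONA trial is designed to show equal results in anatomic and clinical success after one year, comparing MOCA with RFA".

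**The concern.** A non-inferiority claim needs evidence that MOCA's success rate is not more than 7 points below that of RFA. The t-test and the Mann-Whitney test ask whether the arms differ at all. Failing to find a difference is compatible with a true deficit larger than the margin, and it becomes more likely as the data become less precise. A pair of Kaplan-Meier curves shows the occlusion rates but contains no decision against the margin.

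So the stated methods do not deliver the conclusion for which the trial was sized. This goes beyond brevity: the section does name tests for one-year data, and those tests fit neither the binary endpoint nor the non-inferiority hypothesis. The abstract's wording about equal results adds to the risk, because it invites a reader to take a non-significant difference as confirmation.

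**Working it through.** **Inputs.** From Sample size calculation: success 93% in both arms, margin 7 points, alpha 5%, power 80%, 210 per group. From Figure 1: 230 per arm, so allocation is 1:1. The results below use 210 evaluable patients per arm.

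**1. The plan's own figure.** Normal approximation with unpooled variance:

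n per group = 2 × 0.93 × 0.07 × (z₁₋α + z₀.₈₀)² / 0.07²

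- One-sided 2.5%: 0.1302 × (1.9600 + 0.8416)² / 0.0049 = 0.1302 × 7.849 / 0.0049 = 208.6, so 209. This agrees with the stated 210.
- One-sided 5%: 0.1302 × (1.6449 + 0.8416)² / 0.0049 = 0.1302 × 6.183 / 0.0049 = 164.3, so 165. This does not agree.

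The stated 210 is therefore the size for a margin test at one-sided 2.5%, which is the same as setting the limit of a two-sided 95% confidence interval against the margin. The analysis section does not name that test.

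**2. The named tests and the margin test can disagree.** Take an illustrative result of 186/210 (88.6%) for MOCA and 195/210 (92.9%) for RFA.

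- Difference: 0.8857 − 0.9286 = −0.0429, or −4.3 points.
- On the 0/1 data, the t-test and the Mann-Whitney test (without continuity correction) both give p = 0.13.
- Standard error: √(0.8857 × 0.1143/210 + 0.9286 × 0.0714/210) = 0.0282.
- 95% confidence interval: −0.0429 ± 1.96 × 0.0282, or −9.8 to +1.3 points.

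The difference is not significant, yet the lower limit is below −7 points, so non-inferiority is not shown.

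**3. How often this matters.** Exact binomial enumeration with 210 per arm and RFA at 93%. The no-difference test is the pooled z-test at two-sided 5%. The margin test requires the lower Wald 95% limit to exceed −7 points.

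| True MOCA rate | No-difference test not significant | Margin test declares non-inferiority |
|---|---|---|
| 86% (at the margin) | 34.6% | 2.9% |
| 85% (beyond the margin) | 24.5% | 1.3% |
| 93% (equal) | 95.2% | 80.6% |

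The 2.9% is the exact rate of the Wald interval, whose nominal level is 2.5%. The normal approximation agrees with the first column: a two-sided 5% test of 93% against 86% has about 65% power at 210 per group, and 80% power would need 300 per group.

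**4. Power of the margin test at the planned size.** Standard error under equality: √(0.1302/210) = 0.0249. Power = Φ(0.07/0.0249 − 1.96) = Φ(0.851) = 80.3% by the normal approximation, and 80.6% by exact enumeration of the Wald interval.

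**The case against.** The strongest objection is that the t-test sentence was never meant for occlusion. Choosing a test by normal or skewed distribution makes sense only for continuous scores such as the VCSS, AVVQ and SF-36, and occlusion has its own sentence. This reading is plausible, and for pain and the continuous scores the tests are suitable. But the sentence covers the one-year data without restriction. If occlusion is taken out of it, all that remains for the primary endpoint is a display. On either reading nothing is compared with the margin.

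A second objection is that a condensed article may leave the confidence-interval method to an analysis plan that is not shown. That plan may well contain the margin test, so the point concerns the published text and not what will finally be done. It still stands, because the text names methods for one-year data that do not match its own design.

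Three stronger readings are tempting and are not supported:

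- **That the plan treats p > 0.05 as proof of equality.** No section states such a rule. The sample size section and the Discussion both speak of non-inferiority. The 34.6% and 24.5% are consequences only if someone applies that rule.
- **That the Kaplan-Meier curves bias the one-year result.** Duplex is done only at scheduled visits, so failure times are known only to an interval. But the curves are stated as presentation, and the article gives no visit windows and no rule for event dates. Any size put on a bias would rest on invented visit scatter. With nominal visit times and no dropout, the curve equals the visit-based proportion.
- **That alpha is left open.** Sidedness is not stated, but the figure of 210 settles it at one-sided 2.5%.

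**Conclusion.** The point holds for the published text. The design and sample size require one-year anatomical success to be tested against a 7-point margin, and the analysis section names no method that does so. A non-significant result from the tests it does name would not establish non-inferiority.

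The size is conditional. If non-significance were taken as the abstract's equal result, which the plan does not say, a treatment truly at the margin would pass in about 35% of trials instead of about 2.9%. Those figures assume 210 evaluable per arm, RFA at 93%, a pooled z-test for no difference and a Wald interval for the margin.

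The sample size is not in error on this point. The 7-point margin was set for anatomical success, and the article gives none for clinical success, so the conclusion here is limited to the anatomical endpoint.

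**What to change.** In Statistical analyses, state that:

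- one-year anatomical success is compared as a difference in proportions, MOCA minus RFA, with a two-sided 95% confidence interval (one-sided 2.5%, the level that reproduces 210);
- non-inferiority is declared only if the lower limit lies above −7 percentage points;
- the t-test and the Mann-Whitney test apply to pain and the continuous scores;
- Kaplan-Meier curves of occlusion are descriptive only.

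In the abstract, replace the wording about equal results, for anatomical success, by non-inferior within 7 percentage points.

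The cost is wording only. The number of patients does not change: with a Wald interval, exact power is 80.6% at 210 evaluable per arm. If the analysis plan that is not shown already contains this test, the article's text needs only to be brought into line with it.

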### Recruitment

A total of 460 patients with primary great saphenous incompetence are to be included in the MARADONA trial after signing informed consent (Figure 1). The pre-procedural status will be determined by the Clinical Etiology Anatomy Pathophysiology (CEAP) score [25] and VCSS [26].

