### Definitions of terms used for the study

Anatomical success: occlusion of the treated GSV segment, measured with duplex.

Clinical success: objective improvement of clinical outcome after treatment, measured with the Venous Clinical Severity Score (VSCC) of at least 1.

Technical success: initial technical success rate of the procedure, where the catheter can be safely placed at a defined distance from the saphenofemoral junction and the GSV can be treated without technical problems.

Failure of treatment: type 1 (non-occlusion) - the treated vein failed to occlude initially and never occluded during the follow-up; type 2 (recanalization) - the treated vein occluded directly after treatment, but recanalized, partly (>10 cm) or completely, at a later time point during follow-up; type 2a - recanalization of the entire treated segment of the vein; type 2b - partial recanalization (open segment > 10 cm).

Post-procedural complications: complications occurring within 30 days after treatment. Major complications to include deep venous thrombosis, pulmonary embolism, skin burn, saphenous neuralgia. Minor complications to include ecchymosis, superficial phlebitis, hyperpigmentation, induration, wound infection of the puncture site, prolonged pain > one week. Sclerosans-related complications.

Operation time: time of the procedure, starting from puncture of the vein to extracting of the catheter, skin-to-skin contact.

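### The named t-test or Mann-Whitney comparison omits centre and baseline score, which costs precision on the continuous scores but does not threaten type I error

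*Protocol article*

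**What the plan says.** The Statistical analyses section states that "Data concerning the one, two and five year follow-up will be analyzed for both study groups" on an intention-to-treat basis "by student t-test (normal distribution) of Mann Whitney U-test (skewed distribution" (I read the linking word as *or*). For occlusion it adds that "Obliteration rates will be presented as Kaplan Meier curves including censoring". It mentions neither centre nor any baseline value, and does not say whether follow-up scores or changes from baseline are compared.

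Other sections describe design features and data that this analysis does not use:

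- Randomization: "Randomization will be performed by blocks with stratification for participating centers". The Setting section lists five centres.
- Recruitment: "The pre-procedural status will be determined by the Clinical Etiology Anatomy Pathophysiology (CEAP) score [25] and VCSS [26". Table 1 repeats CEAP/VCSS at each follow-up visit.
- Quality of life scores: "Both questionnaires are completed preoperatively, after 4 weeks, one, two, and five years of follow-up".

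The Definitions section gives clinical success as "objective improvement of clinical outcome after treatment, measured with the Venous Clinical Severity Score (VSCC) of at least 1" and anatomical success as "occlusion of the treated GSV segment, measured with duplex".

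**The concern.** Stratifying by centre removes most between-centre variation from the treatment contrast. A two-sample test that ignores the strata counts that variation as noise, so its standard error is larger than the design warrants. Separately, when a score is measured before treatment and again at follow-up, the baseline value usually predicts part of the follow-up value. An analysis that leaves it out pays for variation that could have been explained, and lets chance baseline differences between arms add to the error of the contrast.

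What is at stake is the width of the intervals for the continuous scores, chiefly the AVVQ, since disease-specific quality of life is a named secondary endpoint. In addition, a Mann-Whitney test on its own gives no treatment difference on the score scale. That sits awkwardly with a trial whose aim includes showing comparable results.

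**Working it through.** **1. The plan's own sample size.** Inputs from the Sample size calculation section: success 93% in both arms, margin 7 points, power 80%, alpha 5%.

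n per arm = (1.960 + 0.842)² × (2 × 0.93 × 0.07) / 0.07² = 7.85 × 26.57 = 208.6, so 209 against the stated 210. This uses one-sided 2.5%. One-sided 5% would give (1.645 + 0.842)² × 26.57 = 164.3, so 165, which does not match. For dropout, 209 × 1.1 = 229.9, so 230 as stated; 210 / 0.9 = 233.3, so 234, is close.

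This figure rests on a binary endpoint with no baseline value of the same measure, so nothing below changes it.

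**2. Where a baseline value can help.**

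- Anatomical success: binary, no baseline counterpart.
- Clinical success: binary, defined by improvement in VCSS, so it already uses baseline.
- Pain: Table 1 lists no screening pain score.
- AVVQ, SF-36 and any continuous VCSS comparison: baseline available. Here the gain applies.

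**3. Size of the baseline gain.** Let r be the correlation between baseline and follow-up, with equal variances at both times. Relative to an unadjusted follow-up comparison (variance 1), the variance is 2(1 − r) for change scores and 1 − r² for ANCOVA. Because 1 − r² = (1 − r)(1 + r) and 1 + r ≤ 2, ANCOVA is never less precise than change scores. The power column takes a comparison with 80% power unadjusted: Φ[(1.960 + 0.842)/√(1 − r²) − 1.960]. The last column is 210 × (1 − r²), rounded up.

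| r (assumed) | Change score | ANCOVA | ANCOVA SE ratio | Power | Adjusted n per arm matching 210 unadjusted |
|---|---|---|---|---|---|
| 0.3 | 1.40 | 0.91 | 0.95 | 84% | 192 |
| 0.5 | 1.00 | 0.75 | 0.87 | 90% | 158 |
| 0.7 | 0.60 | 0.51 | 0.71 | 98% | 108 |

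These factors apply to the t-test route. They do not measure a rank test on skewed scores.

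**4. Does omitting baseline invalidate the standard error?** No. In a simulation with 420 patients, no centre effect and r = 0.5, the t-test's average model standard error was 0.0975, the empirical one was 0.0985, and type I error was 5.0%.

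**5. Size of the centre effect.** Assumed: five centres of 150, 100, 80, 50 and 40 patients and blocks of 4. The intraclass correlation (ICC) is also assumed. The sum of squared centre shares is (22,500 + 10,000 + 6,400 + 2,500 + 1,600) / 420² = 43,000 / 176,400 = 0.244. The pooled variance seen by the t-test is then about (1 − ICC) + 0.756 × ICC, whereas the contrast really varies with 1 − ICC. The standard error ratio is the square root of their quotient; at ICC 0.10 it is √(0.9756 / 0.90) = 1.041.

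| ICC (assumed) | SE ratio, formula | SE ratio, simulated | Type I error of t-test, simulated |
|---|---|---|---|
| 0.01 | 1.004 | 1.00 | 4.9-5.0% |
| 0.05 | 1.020 | 1.01-1.02 | 4.4-4.9% |
| 0.10 | 1.041 | 1.04 | 4.2% |
| 0.20 | 1.090 | 1.08-1.10 | 3.3-3.4% |

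Monte Carlo error on the type I rates is about 0.8 points (3,000 replicates). With no centre effect, where the SE ratio should be 1, the simulation gave 1.030 and 0.990, so single simulated ratios are uncertain by a few hundredths. The formula gives the same picture without that noise.

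**The case against.** The strongest objection is that a journal article's short statistics section is a summary, and that covariates and model form normally sit in a fuller analysis plan. A t-test is legitimate and contradicts nothing else in the article. That would settle the matter if the section were silent. It is not: it names a method, and a better one is available from the planned data. A fuller plan may already contain adjusted models, in which case the article's wording only needs to be aligned with it.

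Several limits on the point stand:

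- The baseline argument reaches none of the three primary endpoints (step 2).
- Among the named secondary endpoints it mainly concerns the AVVQ. The SF-36 is described as a general health measure, and a continuous VCSS comparison is not a named endpoint.
- The test sentence covers one, two and five years and assigns no test to two-week pain. Adding centre there is an extension of the point.
- For skewed scores a rank test can be a reasonable choice. The table in step 3 does not show otherwise.

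Two stronger readings are tempting. A reader might infer that the planned tests give invalid standard errors or p-values. They do not: omitting baseline leaves the unadjusted standard error valid, and omitting centre errs on the conservative side. A reader might also infer that raw follow-up scores will certainly be compared with baseline ignored. The article does not say so. If changes are analysed, baseline is partly used, though less efficiently than by ANCOVA.

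**Conclusion.** The point holds as one of efficiency and consistency with the design. On the continuous scores, the named t-test gives away 9% to 49% of the variance relative to ANCOVA for r between 0.3 and 0.7 if follow-up values are compared. If changes are compared, it is still no more precise than ANCOVA. Leaving out centre makes standard errors about 0-4% too large at an ICC up to 0.10 and 8-10% too large at 0.20; type I error stays at or below the nominal level. The size of 210 (230) per arm stands.

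Both r and the ICC are assumptions, as are the centre sizes and block length; the article gives none of them. The direction of each effect does not depend on the exact values, but the size does.

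**What to change.** Amend the Statistical analyses section so that:

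1. continuous AVVQ and SF-36 scores, and any continuous VCSS comparison, are analysed by ANCOVA or a repeated-measures mixed model with baseline score, centre and treatment, reporting the adjusted difference with a 95% confidence interval;
2. the pain comparison includes centre;
3. anatomical and clinical success are each estimated as a centre-stratified risk difference (for example, Mantel-Haenszel) with a 95% confidence interval;
4. rank tests are kept as sensitivity analyses.

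The cost is analysis wording only. Centre and the baseline scores are already part of planned data collection, and no change in sample size or visits is needed. The Trial status section reports 50 of the planned 460 patients randomised by December 2013, so at that stage the change could be fixed well before the one-year results.
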